### Implementation {16c}

The principal research [name] will generate the allocation sequence, enrol participants, and assign participants to either control group or intervention group.

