**Methods:**

A quantitative approach will be adopted using a randomized pre-test and post-test experimental design in a medical centre in northern Taiwan. The web-based decision aid consists of five sections. Section 1 provides a two-part video to introduce SDM and how to participate in SDM. Section 2 presents an overview of functions and features of the birth decision-aid. Section 3 presents relevant VBAC information, including definitions, benefits and risks, and an artificial intelligence (AI) calculator for rate and likelihood of VBAC success. Section 4 presents the information regarding elective repeat caesarean delivery (ERCD), involving definitions, benefits, and risks. Section 5 comprises four steps of decision making to meet women’s values and preferences. Pregnant women who have had one previous caesarean and are eligible for VBAC, will be recruited at 14–16 weeks. Participants will complete a baseline survey prior to random allocation to either the control group (usual care) or intervention group (usual care plus an AI-decision aid). A follow up survey at 35–38 weeks will measure change in decisional conflict, knowledge, birth mode preference, and decision-aid acceptability. Actual birth outcomes and satisfaction will be assessed one month after birth.

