### Eligibility criteria {10}

Using purposive sampling, the selection criteria includes women aged between 20 and 45; have experienced one previous CD; 14–16 weeks’ gestation with at least a half year interval between current pregnancy and the previous birth; and are fluent in English or Mandarin. Exclusion criteria includes women with multiple pregnancy, previous classic CD, or myomectomy, and/or pregnancy with high risk of complications (for example, women who had risk factors such as hypertension, heart disease, diabetes, epilepsy, threatened premature labor, or another preexisting medical problem).

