### Who will take informed consent? {26a}

The principal researcher [name] will invite eligible women to participate in the study. Prior to the study commencement, the participants will give written informed consent for participation after the principal researcher explain the purpose and procedure of the study.

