### Participant timeline {13}

Eligible women will be invited to participate in the study when they attend prenatal examination at the 14–16 weeks’ gestation visit in the Outpatient Department of Obstetrics and Gynecology within the hospital study site. After participants sign written consent for participation, they will be randomly allocated to either the control group or intervention group by the principal researcher. All participants will initially complete an online google survey including ‘personal demographic information’, ‘decision conflict scale’ ‘knowledge scale’ and ‘birth mode preference’. After completing the questionnaires, women allocated to the intervention group and the principal researcher will provide women a username and password to log into the birth decision-aid platform. The principal researcher will encourage women to discuss information with their families. They will be encouraged to use the decision-aid during recruitment and at each visit in the hospital Outpatient Department of Obstetrics. To answer questions and clarify information about the decision-aid, an online individual consultation with the principal researcher will be provided for women in the intervention group at least twice during the 17–34 weeks’ gestation. A first-time follow up survey will be held at 35–38 weeks’ gestation, including decision conflict scale, knowledge, birth mode preference, and decision-aid acceptability. All participants confirm preferred birth mode with their obstetrician prior to completing the first-time follow up. A second-time follow up is held one month after birth. Postnatal women will complete a “satisfaction” questionnaire when they attend their postnatal examination visit (Fig. 3).

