## Assignment of interventions: allocation

### Sequence generation {16a}

Using computer permuted block randomization.

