### Concealment mechanism {16b}

A parallel group of participants will be allocated to either control group (usual care) or intervention group (usual care plus the birth decision-aid platform) in a quiet examination room in accordance with sequentially numbered computer permuted block randomization.

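### One person generates the permuted-block sequence, enrols the women and assigns them, so the recruiter can know each upcoming allocation before inviting a woman, and selection bias is open

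*Protocol article*

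**What the plan says.** All references are to the protocol article.

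- **Sequence generation {16a}:** the whole entry is "Using computer permuted block randomization". No block size is given.
- **Concealment mechanism {16b}:** women are allocated "in a quiet examination room in accordance with sequentially numbered computer permuted block randomization".
- **Implementation {16c}:** the principal researcher "will generate the allocation sequence, enrol participants, and assign participants to either control group or intervention group".
- **Who will take informed consent? {26a}:** the same person "will invite eligible women to participate in the study" and explains the study before consent is given.
- **Participant timeline {13}:** after written consent, "they will be randomly allocated to either the control group or intervention group by the principal researcher". The baseline survey is described after this step.
- **Abstract, Methods:** the opposite order is given: "Participants will complete a baseline survey prior to random allocation".
- **Who will be blinded {17a}:** participants are to be blinded after assignment, and data entry and analysis are to be blinded. The recruiter is not mentioned.

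**The concern.** Random allocation protects against selection bias only if the person who decides whether and when to approach a woman cannot foresee her arm. Here the person who makes the list also invites, consents and assigns. That person could, without any intent, present the study differently or time an approach differently according to the arm that comes next.

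The primary outcomes are decisional conflict, knowledge, birth mode preference and decision-aid acceptability, all taken from questionnaires that the women complete. Motivation and leaning towards vaginal birth can be sensed in the invitation conversation, and they plausibly relate to all four. If such women went more often to one arm, the groups would differ before the decision aid was opened, and the difference would be read as its effect. Analysis cannot fully repair this, because unmeasured traits stay unbalanced.

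**Working it through.** **Step 1: who does what.**

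| Task | Done by | Section |
|---|---|---|
| Generate the sequence | principal researcher | {16c} |
| Invite and explain | principal researcher | {26a} |
| Enrol | principal researcher | {16c} |
| Assign | principal researcher | {16c}, {13} |
| Hide the next assignment from the recruiter | nothing described | {16b} |

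The first four rows are stated rules. The last row is what the concealment section, which is filled in, does not supply. A numbered list fixes the order of assignments; it does not hide them from its author.

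**Step 2: do other provisions close the gap?** Allocation after consent ({13}) protects only if the person taking consent cannot foresee the result. The blinding in {17a} starts after assignment or concerns data entry and analysis. Neither covers the recruiter before assignment.

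**Step 3: the plan's own sample size.** Inputs from Sample size {14}: effect size 0.50, α = 0.05, power 0.80. A two-sided two-sample t-test with equal arms (noncentral t) needs 63.77, so 64 per arm, 128 in total, with power 0.801. This matches the stated 128. Then 128 × 1.20 = 153.6, so 154, also as stated. If 20% of 154 are lost, 154 × 0.80 = 123.2 remain, or 61.6 per arm. These figures are neither evidence for nor against the point; they set the scale for step 4.

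**Step 4: illustration of what selection could do.** Assume no true effect and a selection-driven difference of δ standard deviations between arms. The values of δ are assumptions; the documents give none. The two-sided 5% t-test then rejects with the probability given by a noncentral t with 2n − 2 degrees of freedom and noncentrality δ√(n/2).

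| δ (assumed) | n per arm | δ√(n/2) | Rejection rate |
|---|---|---|---|
| 0 | either | 0 | 5.0% |
| 0.15 | 61.6 | 0.83 | 13.1% |
| 0.15 | 64 | 0.85 | 13.4% |
| 0.25 | 61.6 | 1.39 | 28.0% |
| 0.25 | 64 | 1.41 | 28.9% |

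The calculation compares follow-up scores without baseline adjustment.

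**Step 5: why varying block sizes belong in the repair.** Suppose the list is taken away from the recruiter but blocks stay fixed at an assumed size of 4, and the recruiter knows that size and all past allocations. There are 6 possible blocks with 4 positions each, so 24 positions. In 8 of them the remaining assignments are forced: 8/24 = 33.3% known with certainty. Best guessing is right in 17/24 = 70.8%. Moving the list is therefore not enough if blocks are fixed and known.

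**The case against.** Much of the case on the other side is fair.

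- *A reader might infer that every allocation is known before consent.* The article does not say this. It places allocation after consent and nowhere says that the list is consulted at invitation. What it supports is that the recruiter can know.
- *A reader might infer that no concealment device exists.* The article is a condensed account, and {31c} refers to a full protocol. Envelopes or a custodian could be described there, so the accurate statement is that none is described. This does not rescue {16c}: an envelope hides nothing from the person who wrote the list.
- *A reader might take "Using purposive sampling, the selection criteria includes women aged between 20 and 45" as proof that the researcher picks among eligible women.* The phrase only introduces the eligibility criteria, and both {26a} and {13} say that eligible women are invited. It is loose terminology, and the point does not need it.
- *The scales are completed by the women, birth outcome is checked against the medical record, and data entry and analysis are blinded.* All true, but these guard against biased measurement, not biased selection.
- *Three of the four primary outcomes are measured at baseline, so imbalance in them would be visible and partly adjustable.* This stands in part. The statistical methods section does not commit to baseline adjustment, acceptability has no baseline measure, and motivation is not listed among the measures. If the order in {13} is followed, baseline answers are given after assignment and are a weaker check.
- *The shifts in the illustration have no source.* Correct. They show sensitivity and do not estimate the bias.

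**Conclusion.** The point holds. It rests on an explicit rule in {16c}, confirmed by {26a} and {13}: the author of the sequence recruits and assigns. Nothing described in {16b} prevents foreknowledge, and no provision elsewhere makes up for it. The documents do not show that the list was in fact consulted before consent or that any woman was steered.

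The size of any bias cannot be derived from the documents. Under the assumed shifts of 0.15 and 0.25 SD, no true effect and an unadjusted comparison, the nominal 5% error rate would become about 13% and 28–29%. The defect does not depend on those figures. Because analysis cannot restore concealment afterwards, it should be corrected in the conduct of the trial wherever women remain to be enrolled.

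**What to change.** For all women still to be enrolled, amend {16a} to {16c}:

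1. Have the sequence, with randomly varying block sizes, generated and held by a web randomiser, or by an existing team member who neither enrols women nor does the analysis. The blinded analyst must not make the list, since that would break the blinding promised in {17a}.
2. Release each assignment only after consent and the baseline survey are logged, through the web tool or sequentially numbered opaque sealed envelopes.
3. Reconcile the abstract with {13} so that the baseline survey precedes allocation.
4. Report how many women were allocated under the present procedure, and add a sensitivity analysis by period (before and after the change).

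The sample size is unaffected. The cost is a short amendment, which {25} sends to the ethics committee for review and approval, plus modest set-up with existing staff or a free tool. The limit is timing: Trial status puts the start of recruitment in September 2021 and the estimated primary completion in September 2023, so few women may remain. The change protects only those not yet enrolled; for the rest, item 4 is what can be done.

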## Assignment of interventions: Blinding

### Who will be blinded {17a}

Participants will be blinded to their allocation after assignment to interventions. Data entry and analysis will both be blinded.

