### Interventions

#### Explanation for the choice of comparators {6b}

The control group condition is essentially ‘usual care’ and will enable comparison with the experimental condition in regard to the shared decision making intervention only, thereby minimizing the potential impact of any additional variables in the experiment. A maternal health booklet, produced by Health Promotion Administration, Ministry of Health and Welfare, Executive Yuan, Taiwan, will be provided to all women in the study [35]. The 58-page booklet is routinely provided to all women during pregnancy in Taiwan and includes Five (5) “Dos” and “Do nots” during pregnancy. Five (5) “Dos” content includes (1) Do receive prenatal exams according to schedule; (2) Do take good care during pregnancy; (3) Do recognize pregnancy complications; (4) Do know the signs of premature birth; (5) Do know the signs of labor. Five (5) “Do nots” content includes (1) Do not smoke or drink; (2) Do not be exposed to secondhand smoke; (3) Do not take medication without doctor’s orders; (4) Do not choose a C-section to pick the time of birth; (5) Do not use drugs [35]. There is very limited information relevant to mode of birth choice after caesarean.

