### Intervention description {11a}

Women in the intervention group will receive both usual care plus access to the web-based decision-aid and access to on-line support. The web-based decision-aid platform was adapted from the original Birth Choices decision-aid by Shorten et al. [36, 37]. We invited 10 experts to evaluate the decision-aid platform for use in Taiwan, including five clinicians (two obstetricians, one head nurse and two supervisor), three midwives, and two academic professors. They provide feedback after consultation; the content validity was 0.97. The web-based decision-aid consists of five sections (Fig. 2). Based on the previous pilot study findings [35], we developed the platform to ensure women complete section and corresponding steps in sequence rather than skipping decision steps. Section 1 provides a two-part video, consisting of two 10-min segments. Part 1 introduces SDM, addressing how to prepare and participate in the study, and how to communicate with the obstetric provider using three talks (team talk, option talk and decision talk). Part 2 provides information with examples to practice communication skills using a BRAIN framework (benefits, risks, alternatives, intuition, and nothing) decision for a better birth plan [38]. Section 2 presents an overview of functions and features of the birth decision-aid. Section 3 presents relevant VBAC information, including definitions, benefits and risks, and an AI calculator for rate and likelihood of VBAC success [20, 33]. In this section the medical history data for pregnant women using the decision-aid platform will be retrieved from the hospital data Health Information System (HIS) system and transferred securely to the warehouse database through the local server. Simultaneously, using the AI model, the pregnant women’s clinical characteristics entered from the Web page will be integrated, cleaned, and converted into a format that will be used by AI edge computing to predict a personal success rate for vaginal birth. Finally, the results are returned to the database and displayed on the Web page through the RESTful API for the clinical staff to access. Section 4 presents the information regarding ERCD, involving definitions, benefits, and risks. Section 5 comprises four steps of decision making to meet women’s values and preferences. Step 1 consists of an animation, reviewing the benefits and risks of VBAC and ERCD. Step 2 consists of a 12-question quiz designed to measure knowledge about VBAC and ERCD. Step 3 presents 12 values clarification statements (6 for VBAC and 6 for ERCD). Using a 6-point Likert scale for each statement, women will be asked to respond to the question ‘what is important for you’, from very important (6 points) to do not consider (1 point). A score in accordance with women’s values for each option will be calculated immediately. Step 4 is designed to confirm women’s birth mode decision based on the values clarification exercise. The principal researcher will offer 2–3 individual online consultations via Line App to answer questions about the decision-aid and clarify information within the decision-aid. Women will be directed back to their provider for questions specific to their pregnancy and decision making.

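### The protocol claims participant blinding that its own design rules out, and it gives two different orders for the baseline survey and random allocation

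*Protocol article*

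**What the plan says.** On blinding, Who will be blinded {17a} makes two statements. The first concerns the women: "Participants will be blinded to their allocation after assignment to interventions". The second concerns the handling of data: "Data entry and analysis will both be blinded".

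On what each arm receives, Intervention description {11a} says: "Women in the intervention group will receive both usual care plus access to the web-based decision-aid and access to on-line support". Participant timeline {13} adds that, for the intervention arm, "the principal researcher will provide women a username and password to log into the birth decision-aid platform", and that "an online individual consultation with the principal researcher will be provided for women in the intervention group at least twice" between 17 and 34 weeks. Explanation for the choice of comparators {6b} gives controls usual care with the routine maternity booklet, which all women in the study receive. No sham platform or attention control is described.

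On timing, the abstract (Methods) says: "Participants will complete a baseline survey prior to random allocation to either the control group (usual care) or intervention group". Participant timeline {13} says that, once consent is signed, "they will be randomly allocated to either the control group or intervention group by the principal researcher". Only then does it describe the baseline questionnaires.

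**The concern.** A woman who is given credentials, works through a five-section platform and has individual consultations knows what she received. A control woman to whom the study has been explained can tell that she did not receive it. The blinding claim in {17a} is an affirmative statement about a core safeguard against bias, so this is a contradiction in the text and not a detail left to a fuller document.

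All four primary outcomes are completed by the women themselves, and three of them are subjective ratings. A reader who relies on {17a} would credit these results with a protection from response bias that the trial does not have.

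The order of the baseline survey matters for a related reason. The trial is described as a randomised pre-test and post-test design. A pre-test is secure only if it is completed before the arm is known to anyone who could influence it. The article gives two different orders.

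**Working it through.** The blinding claim contains no figure to recompute, so the check sets the sections side by side. A short calculation then gives a sense of scale.

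**Step 1. Can a woman infer her arm?**

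| Element | Intervention | Control | Source |
|---|---|---|---|
| Routine booklet and usual care | yes | yes | {6b}, {11a} |
| Username and password | yes | no | {13} |
| Platform with two 10-minute video segments and a calculator of VBAC success | yes | no | {11a} |
| Individual online consultations with the principal researcher | at least two | no | {13} |
| Sham or attention control | – | none described | {6b} |
| Study explained before consent | yes | yes | {26a} |

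Every element that separates the arms is visible to the woman. Nothing in the article hides the difference.

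**Step 2. Do other sections depend on the claim?** Yes. Section {11b} provides for telling intervention women their allocation if an emergent situation arises. Section {17b}, headed as an unblinding procedure, covers the same situation. Both presume that women already using the platform do not know their arm.

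**Step 3. Is the principal researcher blinded?** No. The same person generates the sequence, enrols and assigns ({16c}), consults with the intervention arm ({13}) and shares data collection with an assistant ({18a}).

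**Step 4. Which outcomes are exposed?**
- Decisional conflict: 5-point agreement items. Subjective.
- Birth mode preference: a 15-point strength rating. Subjective.
- Decision-aid acceptability: nine items rating the platform itself. Subjective.
- Knowledge: 15 items scored +1, 0 or −1 against a correct answer. Less exposed to reporting bias.
- Satisfaction with the decision (secondary): a self-rating, so exposed.
- Actual birth outcome (secondary): verified with the medical record, so not a matter of self-report alone.

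**Step 5. Order of baseline and allocation.** The abstract gives survey, then allocation. Section {13} gives consent, allocation, survey and login, in that order. The two cannot both describe the procedure. In {13} the login comes after the questionnaires, and no sentence says that women are told their arm before answering. What {13} does imply is that the principal researcher knows the arm by then.

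**Step 6. Scale, as an assumed illustration.** The plan's sample size reproduces. A two-sample t-test with d = 0.50, α = 0.05 (two-sided assumed, as the article does not say) and power 0.80 needs 63.77, rounded up to 64, per arm. That is 128 in total, with power 0.801. Then 128 × 1.2 = 153.6, rounded up to 154.

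Now suppose there is no true effect, but knowledge of the arm shifts self-ratings by b SD. With 64 per arm (126 degrees of freedom), the noncentrality is b × √(64/2) = b × √32.

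| Assumed b (SD) | Noncentrality | Chance of p < 0.05 |
|---|---|---|
| 0 | 0 | 5.0% |
| 0.1 | 0.57 | 8.7% |
| 0.2 | 1.13 | 20.2% |
| 0.3 | 1.70 | 39.1% |

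The values of b are not in the article. The table shows only that a modest bias would matter at this sample size.

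**The case against.** The strongest reply is that open-label delivery is hard to avoid when a decision aid is compared with usual care. The article also describes that delivery openly, so an attentive reader would not be misled for long. Correcting the sentence would change neither the sample size nor the planned analyses. The first part stands: unmasked delivery is not the error. The error is the claim of blinding, together with the two sections built on it.

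A reader might infer several stronger points that the documents do not support.
- *Blinding of data entry and analysis has failed.* This is not shown. Acceptability data could reveal the arm, since controls have no platform to rate. But {13} does not limit that questionnaire to one arm, and {20b} plans to compare it between arms. Analyst blinding is at risk and needs a safeguard.
- *Women answered the baseline survey knowing their arm.* No section says so.
- *All four primary outcomes are equally compromised.* Knowledge is scored against correct answers.
- *A baseline-adjusted analysis is biased.* Section {20a} lists bivariate analyses, linear regression and a signed-rank test. It names no analysis of covariance, so no effect on such a model can be claimed.
- *The bias has a known size.* It does not, and the article does not say to which outcome the planned effect of 0.50 belongs.

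**Conclusion.** The point holds in two parts.

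First, participant blinding as stated in {17a} does not exist. This follows from {26a}, {6b}, {11a} and {13} together and needs no outside source. Decisional conflict, birth mode preference and acceptability are therefore open-label self-reports, and so is the secondary satisfaction score. Knowledge is less exposed. The conclusion would soften only if the trial withheld its hypothesis or arm labels from women. The article does not say that it does, and its consent section points the other way.

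Second, the abstract and {13} disagree on whether the baseline survey precedes allocation. Baseline may not be a secure pre-randomisation measure; that it was contaminated is not established.

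The size of any reporting bias cannot be derived from the article. The range of 9% to 39% shown above rests wholly on assumed biases of 0.1 to 0.3 SD, 64 analysed per arm and a two-sided test. The separate statement that data entry and analysis are blinded is not disproved.

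**What to change.** - **{17a}:** state that participants and the principal researcher are not blinded.
- **{11b} and {17b}:** reconcile both with the corrected {17a}, since each presumes that women do not know their arm. What should happen clinically in those situations is for the investigators to settle.
- **{13}:** state that randomisation follows submission of the baseline survey, as the abstract already says. Recruitment began in September 2021 (Trial status), so the order actually used for women already enrolled should be documented and reported.
- **Data handling:** keep data entry and analysis on coded arms. Hold acceptability and platform data in a separate file, because they could reveal the arm.
- **Reporting:** present the self-reported outcomes as an open-label comparison and acknowledge possible reporting bias, noting that knowledge is less exposed.

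The cost is mostly wording, plus the order of two steps in one visit and one separate data file. The sample size is unaffected. The trial gives up a claimed strength. If {13} describes what has been done so far, changing the order now would leave two procedures within one trial, which is why the order used for each woman should be recorded.
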